# Differences in Messenger RNA Expression of Fibulin-1, Elastin, Matrix Metalloproteinase-1, Basic Fibroblast Growth Factor, and α-Smooth Muscle Actin Between the Ventral and Dorsal Tunica Dartos in Patients With Hypospadias and Chordee: Protocol for a Prospective Cohort Study

**DOI:** 10.2196/52282

**Published:** 2024-10-30

**Keywords:** chordee, gene expression, hypospadias, polymerase chain reaction, mRNA

## Abstract

**Background:**

Hypospadias is a common congenital anomaly characterized by the displacement of the urethral opening to the ventral side of the penis. Surgical correction is often necessary for functional and psychological reasons. The etiology involves genetic and environmental factors, and chordee, a downward curvature of the penis, is a common complication. Proteins such as fibulin-1, elastin, matrix metalloproteinase-1, basic fibroblast growth factor, and α-smooth muscle actin play roles in hypospadias development.

**Objective:**

The study’s aim is to investigate the differences in messenger RNA (mRNA) expression of fibulin-1, elastin, matrix metalloproteinase-1, basic fibroblast growth factor, and α-smooth muscle actin between the ventral and dorsal tunica dartos in patients with hypospadias and chordee.

**Methods:**

This prospective cohort study aims to investigate differences in mRNA expression of the abovementioned proteins between the ventral and dorsal tunica dartos in patients with hypospadias and chordee. Ethics approval has been obtained, and consent from parents will be obtained before data collection. Eligible participants are aged 6-18 months, diagnosed with hypospadias and chordee, and planned for urethroplasty. Tissue samples will be collected from both aspects of the tunica dartos and analyzed using real-time quantitative reverse transcription–polymerase chain reaction. Data analysis will involve statistical tests and normalization of housekeeping genes.

**Results:**

This study is at the protocol development stage. A pilot study regarding its feasibility has been ongoing as of August 2023. The study results are expected to be available by the end of 2024.

**Conclusions:**

The study of mRNA expressions of various proteins in the tunica dartos of patients with hypospadias and chordee is expected to improve the understanding and expand the knowledge of the pathophysiology of hypospadias and chordee.

**International Registered Report Identifier (IRRID):**

DERR1-10.2196/52282

## Introduction

Hypospadias is one of the most common congenital anomalies in male neonates. It is characterized by the urethral opening being misplaced on the ventral side of the penis instead of the tip. Its prevalence globally is around 1 in 200-300 male births [1]. It has significant psychological and functional impacts, requiring surgical correction to achieve normal appearance and function. Various surgical techniques exist, but controversies persist regarding the best approach for different types of hypospadias [2]. The etiology of hypospadias is believed to be multifactorial, involving genetic and environmental factors [3,4]. Chordee, a downward curvature of the penis, is commonly associated with hypospadias and results from tissue growth disturbances [5].

The proteins fibulin-1, elastin, matrix metalloproteinase-1 (MMP-1), basic fibroblast growth factor (bFGF or FGF-2), and α-smooth muscle actin (α-SMA) play roles in hypospadias development [4,6,7]. Fibulin-1 is related to extracellular matrix integrity, while elastin contributes to tissue extensibility. MMP-1 is involved in matrix remodeling, while bFGF affects differentiation. α-SMA is implicated in fibrosis. Messenger RNA (mRNA) expression of these proteins may shed light on their roles in hypospadias [2,4,8].

However, research on dartos tunic elasticity, genetic factors, and mRNA expression in hypospadias is limited. A better understanding of the genes influencing dartos tunic elasticity could provide insights into pathophysiology and chordee management. Therefore, this protocol is designed to investigate the differences in mRNA expression of fibulin-1, elastin, MMP-1, bFGF, and α-SMA between the ventral and dorsal tunica dartos in patients with hypospadias and chordee.

## Methods

### Study Design

This is an observational study using a prospective cohort, designed for the investigation of the differences in mRNA expression of fibulin-1, elastin, MMP-1, bFGF, and α-SMA between the ventral and dorsal tunica dartos in patients with hypospadias and chordee. The protocol is prepared according to the SPIRIT (Standard Protocol Items: Recommendations for Interventional Trials) 2013 checklist for reporting a protocol study [9].

### Ethical Considerations

This study was conducted in accordance with the principles outlined in the Declaration of Helsinki. The approval for the protocol of this study was granted by the Medical Research Ethics Committee, Universitas Indonesia, in April 2022 (KET-413/UN2.F1/ETIK/PPM.00.02/2022). All participants provided written informed consent prior to their inclusion in the study, and the study protocol was reviewed and approved by the institutional review board to ensure ethical standards and participant safety.

Informed consent was obtained from all participants during the primary data collection phase. The original informed consent covered the possibility of secondary data analysis, and the institutional review board confirmed that no additional consent was required for this study’s secondary analysis.

To ensure the privacy and confidentiality of participants, all study data were deidentified prior to analysis. Personal identifiers were removed, and the data were anonymized to protect the participants’ identities. Appropriate measures were taken to maintain the confidentiality of the data throughout the study.

No additional compensation was provided for this analysis as it did not involve additional participant interaction.

There are no images included in the manuscript or supplementary material that could potentially identify individual participants. If such images are deemed necessary in future submissions, we will ensure that consent has been obtained from identifiable individuals, and relevant consent forms will be uploaded during resubmission.

Consent for the data collection and publication has been obtained from the parents of patients with hypospadias. The consent was sought after the parents and their children have already received an explanation from the main researcher.

The data taken for this study were stored and uploaded over the internet without any identifier.

### Eligibility Criteria and Recruitment Procedures

The eligibility criteria for participants in this study are as follows:

Inclusion criteria:Diagnosed as having hypospadias with chordee by a pediatric urologistAged 6-18 monthsPlanned to undergo urethroplastyExclusion criteria:The amount of available tissue specimens is insufficient for further examinationPatients with genital ambiguity characterized by clitoral hypertrophyThe patient is experiencing an infection of the prepucePatients with a history of previous chordectomy or urethroplasty surgeryPatients with conditions that can experience dysregulation of extracellular matrix component proteins, namely malignancy and Marfan syndrome

Participants for this research will be enrolled through a consecutive recruitment method. Parents of eligible patients will receive information about the study’s procedures and will be given the opportunity to decide whether they wish for their children to take part in the study during its duration.

### Clinical Outcomes

The clinical outcomes measured in this study are as follows:

Expression of fibulin-1 mRNAExpression of elastin mRNAExpression of MMP-1 mRNAExpression of bFGF mRNAExpression of α-SMA mRNA

The clinical outcomes will be measured from differences in mRNA expression from both the dorsal and ventral aspects of the tunica dartos excised during urethroplasty. A positive control gene for both dorsal and ventral tissues will also be measured in subsequent analyses. The expression levels of the 5 genes will be assessed relative to the housekeeping gene β-actin using fold change values.

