#### Quantification of RNA and Circular DNA Synthesis

The quantification stage serves to determine the RNA concentration in each sample in order to dilute them to the same concentration, which is 0.2 ng/µL. RNA quantification from each sample and control will be performed using the Qubit dsDNA HS kit (Q32851; Thermo Fisher Scientific). All samples from the whole genome amplification stage are vortexed and diluted by mixing 5 µL of the sample with 45 µL of double-distilled water to achieve a 1:10 dilution. Samples, controls, and the Qubit standard solution are placed in 500-µL tubes containing Qubit dsDNA reagent with specific volumes.

All samples are then vortexed, spun down, and incubated at room temperature for 2 minutes. The RNA quantification results are then used for circular DNA synthesis using the cDNA Taqman MicroRNA Reverse Transcription Kit (4366596; Thermo Fisher Scientific). The composition of the reagents used can be seen in Hidayati et al [10]. The master mix, containing the samples, is then incubated in a thermal cycler.

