#### Data Analysis

The amplification curve data will then be analyzed to determine the cycle threshold (Ct) value. The Ct values are then normalized to that of the housekeeping gene to calculate the relative gene expression using the ΔΔCt method.

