### Data Analysis

The data to be collected in this study include clinical characteristics such as age, height, weight, BMI, comorbidities, and delivery history, accompanied by mRNA expression from both the dorsal and ventral sides of the tunica dartos tissue.

All quantitative data obtained from this research will be analyzed using SPSS (version 25.0; IBM Corp) software. The normality of all numeric data will be tested using the Kolmogorov-Smirnov test. Numeric data will be presented as mean (SD) for normally distributed data and median (range) for nonnormally distributed data.

If the obtained data are normally distributed, an independent 2-tailed *t* test will be performed. Meanwhile, nonnormally distributed data will be tested using the Mann-Whitney *U* test to determine gene expression differences between research groups. The quantification of gene expression is expressed as fold change, compared to the housekeeping gene used in the study.

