Notable distinctions in collagen and elastin content are observed between normal and hypospadias-afflicted penises, affecting the stiffness and flexibility of the tunica dartos [7]. There are some proteins that play roles in the elasticity of a tissue. Elastic connective tissue is pivotal in various pathological tissue changes. Elastin, an essential component of the extracellular matrix, endows tissues with extensibility and elasticity. Low elastin concentrations are linked to impaired male urethral development, while elastin-rich concentrations in male fetus urethras elevate intrauterine pressure during the early stages of micturition [14]. Matrix metalloproteinases play a key role in embryological processes and wound healing. MMP-1, a collagenase enzyme, breaks down collagen types I, II, and III, influencing extracellular matrix repair. Decreased MMP-1 levels in hypospadias are linked to increased collagen production. Unbalanced collagen synthesis and degradation can lead to fibrotic tissue formation [15]. Fibroblast growth factors regulate fibroblast growth and differentiation. bFGF stimulates cell proliferation and differentiation, impacting the mesodermal, ectodermal, and endodermal areas. Abnormalities in the bFGF pathway contribute to urethral plate formation, potentially resulting in fibrotic tissue development. α-SMA, implicated in fibrogenesis, drives myofibroblast differentiation and extracellular matrix repair. In the context of hypospadias, α-SMA involvement points to fibrocontractive diseases such as chordee [16].

While this study may provide insights into the differences of the ventral and dorsal tunica dartos, we did not include samples of tunica dartos from healthy patients, which would limit the data analysis only to patients with chordee.

Understanding the differential mRNA expression of fibulin-1, elastin, MMP-1, bFGF, and α-SMA between the ventral and dorsal tunica dartos in patients with hypospadias and chordee presents an opportunity to explore the intricate molecular mechanisms underlying hypospadias development and its associated complications.

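### All five outcomes are normalised to β-actin alone with no described check that it is equal on the two sides, so any ventral-dorsal shift in β-actin would bias all five comparisons alike

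*Protocol article*

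**What the plan says.** The Clinical Outcomes section names the reference gene: "The expression levels of the 5 genes will be assessed relative to the housekeeping gene β-actin using fold change values". The laboratory Data Analysis subsection gives the method: "The Ct values are then normalized to that of the housekeeping gene to calculate the relative gene expression using the ΔΔCt method". The statistical Data Analysis section again refers to a single reference: "The quantification of gene expression is expressed as fold change, compared to the housekeeping gene used in the study". For the comparison between sides it says: "If the obtained data are normally distributed, an independent 2-tailed *t* test will be performed". Mann-Whitney is the alternative for non-normal data.

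Two phrases might point to a further control. The abstract says: "Data analysis will involve statistical tests and normalization of housekeeping genes", with genes in the plural. Clinical Outcomes adds: "A positive control gene for both dorsal and ventral tissues will also be measured in subsequent analyses". Neither names a second gene, and neither is tied to normalisation or to comparing β-actin between sides. Table 1 gives primers for the five target genes only.

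**The concern.** ΔΔCt gives the true ventral-dorsal contrast of a target gene only if the reference gene is the same on both sides. Here a single reference enters all five outcomes, so an error in it is shared by all five. Five genes moving together by a similar amount could be read as a coherent biological pattern when it comes from the normaliser. Equally, a real difference in one gene could be cancelled or inflated. A larger sample does not help: the bias stays the same while the standard error shrinks, so a false finding becomes more likely.

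The concern is about an assumption that is not verified, not one shown to be false.

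**Working it through.** The article states no figure on this point, so there is none to reproduce.

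**Algebra.** With V for ventral and D for dorsal,

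ΔΔCt = (Ct_gene,V − Ct_ref,V) − (Ct_gene,D − Ct_ref,D).

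Let Ct_ref,V − Ct_ref,D = d, and let the target gene be truly unchanged (Ct_gene,V = Ct_gene,D). Then ΔΔCt = −d, and the apparent ventral/dorsal fold change is 2^d. The target gene has dropped out, so the result is the same for all five.

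- d = 0.25: 2^0.25 = 1.19
- d = 0.5: 2^0.5 = 1.41
- d = 1: 2^1 = 2.0

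A shift the other way gives the reciprocals (0.84, 0.71, 0.50).

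**Chance that an unchanged gene is declared different.** The test is the planned independent two-sided t test. Everything else is assumed, because the article does not give it: alpha 0.05, n = 20 per side (30 for comparison), SD of ΔCt 1 or 1.5 cycles, analysis on the ΔCt scale, and no correlation between a patient's two samples. The noncentrality is d / (SD × √(2/n)), with 2n − 2 degrees of freedom.

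For n = 20, √(2/20) = 0.316, with 38 degrees of freedom and critical t 2.024. The noncentralities are 0.79, 1.58 and 3.16 at SD 1, and 0.53, 1.05 and 2.11 at SD 1.5.

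| n per side | SD | d = 0.25 | d = 0.5 | d = 1 |
|---|---|---|---|---|
| 20 | 1 | 12% | 34% | 87% |
| 20 | 1.5 | 8% | 18% | 54% |
| 30 | 1 | 16% | 48% | 97% |
| 30 | 1.5 | 10% | 25% | 72% |

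The rates rise with n, as expected for a bias.

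**All five genes together.** In a simulation, five unchanged genes shared one reference (10,000 runs, ΔCt SD 1, independent t test, target and reference variances equal).

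| n per side | Result | d = 0 | d = 0.25 | d = 0.5 | d = 1 |
|---|---|---|---|---|---|
| 20 | at least one gene significant | 20% | 35% | 69% | 99% |
| 20 | all five significant | 0.1% | 0.8% | 7% | 64% |
| 30 | at least one gene significant | 18% | 42% | 82% | 99.9% |
| 30 | all five significant | 0.1% | 1.3% | 15% | 89% |

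The mean bias in each gene equalled −d within simulation error. So the bias is always shared, while joint significance is uncommon unless the shift is large.

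**What a second reference buys.** Normalising to the mean Ct of two references, of which only β-actin shifts, gives a bias of (d + 0)/2 = d/2. A 1-cycle shift then acts like 0.5 cycle (apparent fold change 1.41 instead of 2.0), and a 0.5-cycle shift like 0.25 (1.19 instead of 1.41).

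**The case against.** **The article may not exclude a second control.** The positive control gene is to be measured on both sides, and the abstract's plural could mean more than one reference. A full protocol may also hold a stability check and the β-actin primers, which a condensed article need not print. This stands in part. The right statement is that no check is described, and the missing primer row is a reporting gap, not proof of a poor design. But the article does fix the normaliser, and it fixes one gene.

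**The documents give no evidence that β-actin varies by side.** A reader might infer that it must, because ventral dartos is thought to be fibrotic and the reference is itself an actin. The article does not support that. The objective is non-directional. The statement that it "drives myofibroblast differentiation and extracellular matrix repair" is about α-SMA, a different gene. The collagen and elastin contrast in the Discussion is between normal and hypospadias tissue. The Discussion does describe ventral dartos as inelastic, but it also reports that earlier studies found no ventral-dorsal disparity. This objection stands: what remains is an unverified assumption.

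**The magnitudes are assumed.** Also true; shift, SD and n are all illustrative. A paired test at n = 20, with SD 1 for the within-patient difference, would give higher rates (19%, 57% and 99%), but that is not the planned test.

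**A simple check has limits.** A confidence interval covering zero does not show equality. With 20 pairs and an SD of 1 for the within-patient difference, its half-width is 2.093 × 1/√20 = 0.47 cycle, so a 0.25-cycle shift would usually go unseen. Raw Ct also depends on RNA input. The quantification step aims to "determine the RNA concentration in each sample in order to dilute them to the same concentration, which is 0.2 ng/µL", but the kit it names is a dsDNA kit, so equal RNA input is not assured as written. Switching to another single gene when the interval excludes zero would be data-driven and would repeat the weakness. These points stand and shape the fix.

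**Conclusion.** The point holds as a design weakness that is cheap to repair. All five outcomes depend on one named reference gene, with no described check of its equality between sides. The shared bias follows from the ΔΔCt formula and needs no assumption beyond a shift existing: d cycles in every gene. How often that yields a false positive depends on inputs the article does not give; under those assumed above with n = 20 per side, it ranges from 8% (0.25 cycle, SD 1.5) to 87% (1 cycle, SD 1) per unchanged gene.

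Two stronger readings are not supported: that β-actin does differ between the sides, and that a shift would make all five genes significant together.

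**What to change.** 1. Prespecify at least one non-cytoskeletal reference gene, run on the same cDNA. Normalise to the mean Ct of the references in the primary analysis, and report results for each reference separately as sensitivity analyses. Do not switch normaliser on the strength of the data.
2. Report, with 95% confidence intervals, the within-patient ventral-dorsal difference in β-actin Ct and in the Ct difference between the two references. The second does not depend on RNA input. Read both intervals as estimates, not as proof of equality. Clarify the RNA quantification step, because raw β-actin Ct cannot be interpreted until that is done.
3. State whether the positive control gene in Clinical Outcomes and the plural in the abstract mean a second reference. If so, name it and add its primers and those of β-actin to Table 1.

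The cost is one primer pair and extra wells, with no additional tissue or patient procedure; β-actin Ct is collected already. Averaging two references reduces the bias but does not remove it if one of them shifts, and the contrast between references cannot reveal a shift that both share.

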### Randomization and Blinding

This study is single blinded. The laboratory assistant does not know which aspect of the penis that the specimen belongs to.

### Study Process and Data Collection

#### Specimen Collection

In this study, tissue samples from the dorsal and ventral sides of the tunica dartos will be obtained from patients with hypospadias and chordee. Ventral tunica dartos samples will be taken from each patient by the researcher as the performing operator, ensuring that the size and location of collection are standardized across all patients. The collected portions are shown in Figure 1.

**Figure 1 figure1:**
[figure not shown]
Site of tissue sample collection from the dorsal and ventral sides of the tunica dartos from patients with hypospadias and chordee, from an observational study conducted in Arifin Achmad General Hospital Riau in 2023 (source: personal documentation of the researcher).

#### Total RNA Isolation

RNA will be isolated from all samples using the RNeasy Mini Kit (Qiagen) following the kit’s manual instructions. Initially, β-mercaptoethanol and ethanol are added to Buffer RPE. Tissue samples are separated from RNAlater stabilization and then mixed with Buffer RLT. For tissue weighing 20-30 mg, 600 µL of Buffer RLT is added. Sample disruption and homogenization are performed using an ultrasonic disruptor tool for 20-40 seconds. The lysed samples are centrifuged at 17,000×g for 3 minutes, and the supernatant is collected for RNA extraction. Then, 70% ethanol, equal to 1× the lysate volume, is added and homogenized using a micropipette.

A total of 700 µL of the sample is transferred to a QIAamp spin column placed in a 2-mL collection tube and centrifuged at >8000×g for 1 minute. The supernatant is discarded, and the process is repeated by pairing a new 2-mL collection tube with the QIAamp spin column until all lysates, including precipitates, are processed. The supernatant and 2-mL collection tube are discarded. The QIAamp spin column is then transferred to a new 2-mL collection tube.

Buffer RW1 (700 µL) is added to the QIAamp spin column and centrifuged at >8000×g for 1 minute. The supernatant and 2-mL collection tube are discarded. This step is repeated with the addition of 500 µL of Buffer RPE. The QIAamp spin column is then combined with 500 µL of Buffer RPE and centrifuged at 17,000×g for 3 minutes, and the supernatant is transferred to a new 2-mL tube and centrifuged at 17,000×g for 1 minute. The QIAamp spin column is moved to a new 1.5-mL microcentrifuge tube, and 30-50 µL of RNase-free water is added directly to the QIAamp membrane, followed by centrifugation at >8000×g for 1 minute.

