#### Expression Quantification Using a Real-Time Quantitative Reverse Transcription–Polymerase Chain Reaction Machine

A real-time quantitative reverse transcription–polymerase chain reaction (qRT-PCR) machine will be used to perform the qRT-PCR amplification using the primary sequences in Table 1.

The machine monitors fluorescence levels after each PCR cycle to track the amount of amplified DNA in real time.

**Table 1 table1:** Primary sequences of the genes used in the study.

Gene	Nucleotide code	Primary sequence (5’-3’)
Fibulin-1	NM_006486.3	F^a^: GATGGTGTCTCCTGTGAAGATG R^b^: TGATGCATGTATGCCCGATAG
Elastin	NM_000501.4	F: CTGCAAAGGCAGCCAAATAC R: CACCAGGAACTAACCCAAACT
MMP-1^c^	NM_002421.4	F: GCCTTCCAACTCTGGAGTAATG R: GAATGGGAGAGTCCAAGAGAATG
bFGF^d^	NM_001361665.2	F: TGAAACGAACTGGGCAGTATAA R: TTGACCTGACTGTGGAAGAAC
αSMA^e^	NM_001613.4	F: GACCCTGAAGTACCCGATAGA R: CTCAGCAGTAGTAACGAAGGAATAG

^a^F: forward.

^b^R: reverse.

^c^MMP-1: matrix metalloproteinase-1.

^d^bFGF: basic fibroblast growth factor.

^e^α-SMA: α-smooth muscle actin.

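### The written RNA workflow states no genomic DNA removal, names no control that would detect DNA, and measures RNA with a dsDNA kit, so co-purified DNA could bias the ventral/dorsal ratios

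*Protocol article*

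**What the plan says.** In the Protocol article, Total RNA Isolation begins: "RNA will be isolated from all samples using the RNeasy Mini Kit (Qiagen", and adds that the kit's manual is followed. It then sets out lysis, disruption, ethanol, column loading, washing and elution, with volumes, speeds and times. The first wash reads "Buffer RW1 (700 µL) is added to the QIAamp spin column and centrifuged at >8000×g for 1 minute". Two steps with Buffer RPE and a further spin follow, and at elution "30-50 µL of RNase-free water is added directly to the QIAamp membrane". No DNase treatment or other removal of DNA is listed, on the column or in the eluate.

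Quantification of RNA and Circular DNA Synthesis brings all specimens to 0.2 ng/µL. There, "RNA quantification from each sample and control will be performed using the Qubit dsDNA HS kit". It also says "All samples from the whole genome amplification stage are vortexed and diluted", although no such stage is described anywhere else. Controls are mentioned without a type, and the composition of the reverse-transcription reagents is left to a cited paper.

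Clinical Outcomes names one control by type: "A positive control gene for both dorsal and ventral tissues will also be measured in subsequent analyses". No reaction without reverse transcriptase (no-RT) and no no-template reaction is named. Table 1 lists primer pairs for the five targets and none for β-actin, and does not say whether any pair spans an intron or exon junction. On the readout, the article says: "The machine monitors fluorescence levels after each PCR cycle to track the amount of amplified DNA in real time".

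**The concern.** Every outcome is an mRNA fold change between two sides of the same organ. Fluorescence after each cycle cannot separate cDNA from genomic DNA when a primer pair amplifies both. As written, the workflow neither removes co-purified DNA nor names a reaction that would show it.

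Two errors could follow. Similar DNA on both sides adds a constant to both signals and shrinks a real ratio. More DNA on one side can produce a difference where there is none. The second is plausible but unproven here: the Discussion describes ventral dartos as inelastic and links several of the proteins to fibrosis, so the two tissues may not extract alike. The first matters because the Discussion reports that earlier studies found no ventral-dorsal disparity, and a ratio pulled towards 1 would look like confirmation. Blinding the laboratory assistant to the side protects against neither.

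The dsDNA kit adds to the problem. If used as written, it equalises specimens on their DNA content, not their RNA content.

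**Working it through.** The article gives no contamination figure, so there is nothing of its own to reproduce. The check asks which way the bias runs and how large it could be.

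**Model.** Set the dorsal target's cDNA to 1. R is the true ventral/dorsal mRNA ratio. g_v and g_d are amplifiable genomic DNA in the ventral and dorsal reactions on the same scale. A is β-actin cDNA, taken as equal on both sides. Target and β-actin primers are taken to amplify DNA equally well. All values of g and A are assumptions.

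Observed ratio = [(R + g_v)/(1 + g_d)] ÷ [(A + g_v)/(A + g_d)]

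**1. Equal carry-over.** With g_v = g_d = g the β-actin factor is 1, leaving (R + g)/(1 + g). For R = 2:

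| g | Arithmetic | Observed ratio |
|---|---|---|
| 0.01 | 2.01/1.01 | 1.99 |
| 0.10 | 2.10/1.10 | 1.91 |
| 0.25 | 2.25/1.25 | 1.80 |
| 0.50 | 2.50/1.50 | 1.67 |
| 1.00 | 3.00/2.00 | 1.50 |

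**2. Unequal carry-over, no true difference (R = 1).**

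- β-actin very abundant, g_v = 0.5 and g_d = 0.1: 1.5/1.1 = 1.36.
- β-actin very abundant, g_v = 1 and g_d = 0.1: 2.0/1.1 = 1.82.
- β-actin very abundant, g_v = 0.01 and g_d = 0.05: 1.01/1.05 = 0.96.
- A = 10, first two cases: (1.5/1.1) × (10.1/10.5) = 1.31 and (2.0/1.1) × (10.1/11) = 1.67.
- A = 1, first two cases: both 1.00, because the same DNA inflates β-actin equally.

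So normalisation to β-actin removes the false difference only when the target is about as abundant as β-actin. It does not undo the shrinkage in step 1. That shrinkage is small for an abundant target only because g, which is DNA per target copy, is then small.

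**3. Equalising on DNA.** Suppose both sides carry the same DNA amount g, but the ventral specimen holds k times the RNA. With β-actin abundant, the observed ratio becomes (R + g/k)/(1 + g). This is the unequal case again, with g_v = g/k. For R = 1, g = 0.5 and k = 0.5: (1 + 1)/(1 + 0.5) = 1.33. Equal DNA concentration therefore does not make carry-over equal relative to mRNA.

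**4. What a no-RT control would show.** Assuming doubling per cycle, a gap of d cycles between the no-RT and specimen Ct means a DNA share of 2^-d: 50% at d = 1, 12.5% at d = 3, 3.1% at d = 5 and 0.8% at d = 7. At d = 5 the share is 1/32, so g = (1/32)/(31/32) = 1/31. With equal carry-over, a true ratio of 2 then reads (2 + 1/31)/(1 + 1/31) = 63/32 = 1.97.

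**The case against.** The strongest reply is that this argues from silence. The isolation follows a kit manual that is not shown, the reverse-transcription reagents sit in a cited paper, and an article may leave plate controls to the full protocol. Table 1 omits β-actin primers although β-actin is the reference gene, so the article plainly does not list everything planned. Controls of unspecified type are mentioned. Primer pairs that span introns would be largely protected, and the documents do not allow that to be checked.

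Much of this stands. A reader might infer that genomic DNA is certainly left in, that a positive control is the only one planned, and that DNA is in fact counted as mRNA. The documents support none of these as facts.

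The size is also open to challenge. Suppose 1% DNA by mass in an assumed 1-2 ng input. At about 3.35 pg per haploid genome (also an assumption), that is 10-20 pg, or 3-6 genome copies. For a target at 100 cDNA copies, g is 0.03-0.06 and a true ratio of 2 reads 2.03/1.03 = 1.97 to 2.06/1.06 = 1.94. The larger distortions need a transcript present at only a few copies, and nothing in the article says that any of the five is that rare.

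What does not stand is the appeal to condensation. The isolation section is a bench recipe down to tube changes, and someone following it would perform no DNA removal. Naming a dsDNA kit for RNA, and an amplification stage described nowhere else, are errors in the text itself, not omissions.

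**Conclusion.** The point holds in conditional form. The workflow as written states no genomic DNA removal, names no reaction that would detect DNA, and measures RNA with a DNA assay. If any primer pair can amplify genomic DNA, equal carry-over shrinks ventral/dorsal ratios and unequal carry-over can create false ones.

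The size cannot be fixed from the article. It is negligible when DNA is about 1% of the target's cDNA copies or less, and large only when DNA approaches the target's own copy number, which means rare transcripts. The false-difference component also vanishes for a target as abundant as β-actin, provided that the β-actin primers amplify DNA equally well. These figures rest on assumed DNA shares, perfect doubling and equal β-actin mRNA on both sides. The stronger conclusion, that the results will be contaminated, is not supported. The workflow should be changed before specimens are processed, because the remedy is cheap and the bias could not otherwise be measured.

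**What to change.** - **Total RNA Isolation:** add an on-column DNase digestion at the RW1 wash.
- **qRT-PCR section:** make one no-RT preparation per specimen and run it in one PCR well for each gene, including β-actin. Run one no-template well per gene per plate. State whether each primer pair, β-actin included, spans an intron or exon junction.
- **Analysis:** flag a gene's result for a specimen when its no-RT Ct lies within about 5 cycles of the specimen Ct (DNA share of about 3% or more, assuming doubling per cycle). Repeat the comparison without flagged results. The 5-cycle limit is a judgement and should be fixed in advance.
- **Quantification section:** replace the dsDNA assay with an RNA assay, reconcile the reference to a whole genome amplification stage with the rest of the workflow, and say what type the controls are.

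The cost is reagent, a short added step and a small loss of RNA. Before replicates, six genes need 6 wells per specimen, and no-RT wells for every gene make it 12, so specimen wells roughly double. No extra patients are needed.
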